### Eligibility criteria

2.3

The study population consists of patients with histologically or cytologically confirmed locally advanced or metastatic pancreatic adenocarcinoma and must have experienced disease progression after at least one line of standard systemic therapy (Table 1). Additional key inclusion criteria require patients to be between 18 and 75 years of age, have a life expectancy of at least 12 weeks, and maintain an Eastern Cooperative Oncology Group (ECOG) performance status of 0 or 1. Patients must possess at least one measurable lesion according to RECIST version 1.1.

**TABLE 1 T1:** Inclusion and exclusion criteria for patient selection.

Item	Criteria description
Inclusion criteria	
Diagnosis	Histologically or cytologically confirmed locally advanced unresectable or metastatic pancreatic adenocarcinoma
Demographics	Age between 18 and 75 years, male or female
Life expectancy	Life expectancy of at least 12 weeks
Performance status	ECOG performance status of 0 or 1
Prior therapy	Disease progression following standard systemic therapy. Disease progression occurring during or within 6 months of completing adjuvant chemotherapy is considered as failure of one line of systemic therapy
Measurable disease	Presence of at least one measurable lesion according to RECIST v1.1. Longest diameter ≥10 mm if measured by spiral CT or ≥20 mm if measured by conventional CT or MRI.
Organ function	Adequate bone marrow and organ function, defined by laboratory results obtained within 7 days prior to enrollment. Patients must not have received blood transfusion, granulocyte colony-stimulating factor, or other medical supportive treatment within 14 days prior to the first dose of study drug • Hemoglobin: ≥90 g/L • Platelets: ≥75 × 10^9/L • White blood cells: ≥3.0 × 10^9/L • Absolute neutrophil count: ≥1.5 × 10^9/L • Total bilirubin: ≤1.5× ULN (≤3× ULN if liver metastases are present) • ALT and AST: ≤2.5× ULN (≤5× ULN if liver metastases are present) • Creatinine: ≤1.5× ULN.
Informed consent	Voluntary participation with a signed and dated written informed consent form
Exclusion criteria	
Prior malignancy	History of other malignant tumors with disease free survival <5 years. Exceptions include cured basal cell carcinoma of the skin, cured cervical carcinoma *in situ*, and gastrointestinal tumors cured via endoscopic mucosal resection
Prior immunotherapy	Prior treatment with anti-PD-1, or anti-PD-L1 inhibitors
Immunodeficiency	Diagnosis of immunodeficiency diseases or HIV infection
Active infection	Severe uncontrolled acute infection, defined as infection causing a fever >38 °C
Viral hepatitis	Active hepatitis B or hepatitis C infection, defined as: HBV DNA ≥2000 IU/mL (or 1 × 10^4 copies/mL), or HCV RNA ≥ lower limit of detection
Organ dysfunction	Severe hepatic or renal insufficiency
Tuberculosis	Active tuberculosis infection within 1 year prior to the first dose. Patients with a history of active tuberculosis >1 year prior may be eligible if there is no current evidence of active infection as determined by the investigator
Lung disease	History of interstitial lung disease or non-infectious pneumonitis that is symptomatic or may interfere with the assessment of pulmonary toxicity
Cardiac history	History of myocardial infarction within 3 months prior to the first dose
Gastrointestinal disorders	History of chronic diarrhea or presence of complete intestinal obstruction
Autoimmune disease	Active autoimmune disease or a documented history of autoimmune disease with a risk of recurrence (e.g., requiring immunosuppressive therapy after organ transplantation). Exceptions allowed type 1 diabetes mellitus, hypothyroidism requiring hormone replacement only, and skin diseases not requiring systemic treatment (e.g., vitiligo, psoriasis, alopecia)
Corticosteroid use	Current use of systemic corticosteroids (>10 mg/day prednisone equivalent) or other immunosuppressive medications within 14 days prior to the first dose. Exceptions allowed inhaled or topical steroids; adrenal replacement (≤10 mg/day prednisone equivalent); short-term (≤7 days) prophylaxis (e.g., contrast dye allergy) or treatment of non-autoimmune conditions (e.g., delayed-type hypersensitivity)
Severe comorbidities	Presence of other severe acute or chronic medical or psychiatric conditions that may affect organ function, making the patient unsuitable for this trial according to the investigator’s judgment
Concurrent trials	Participation in another clinical trial with an investigational drug within 4 weeks prior to the first dose
Pregnancy and lactation	Women who are pregnant or breastfeeding, or patients of childbearing potential (men or women who have been post-menopausal for less than 1 year) unwilling to use effective contraception methods
Hypersensitivity	History of allergic or hypersensitivity reactions to any study drug components
Investigator judgment	Patients deemed unsuitable for participation in this clinical trial by the investigator

Abbreviations: ALT, alanine aminotransferase; AST, aspartate aminotransferase; CT, computed tomography; ECOG, eastern cooperative oncology group; HBV, hepatitis B virus; HCV, hepatitis C virus; HIV, human immunodeficiency virus; IU, international units; MRI, magnetic resonance imaging; PD-1, programmed cell death protein 1; PD-L1, programmed death-ligand 1; RECIST, response evaluation criteria in solid tumors; ULN, upper limit of normal.

Candidates will be excluded if they have a history of other malignancies within the past 5 years, uncontrolled concurrent illnesses, or significant autoimmune or immunodeficiency diseases.

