### Study objectives

2.1

The primary objective of this study is to evaluate the safety and efficacy of JDB153 tablets combined with serplulimab injection in patients with advanced pancreatic cancer who have experienced disease progression following standard treatments.

The primary endpoints focus on safety profile and objective response. Safety is assessed based on adverse events (AEs) graded via the National Cancer Institute Common Terminology Criteria for Adverse Events (NCI-CTCAE) version 5.0, including the incidence of dose-limiting toxicities (DLTs), serious adverse events (SAEs), and treatment-related adverse events (TRAEs). Efficacy is primarily measured by the objective response rate (ORR), defined as the proportion of patients achieving complete response (CR) or partial response (PR) according to Response Evaluation Criteria in Solid Tumors (RECIST) version 1.1.

Secondary endpoints include the disease control rate (DCR), as well as OS, PFS, duration of response (DoR), and time to progression (TTP). DCR is defined as proportion of patients achieving CR, PR, and stable disease (SD). OS is defined as the time from study enrollment to death from any cause. PFS is defined as the time from study enrollment to the first documented disease progression or death. DoR is defined as the time from first documented objective response (CR or PR) to disease progression or death, and TTP is defined as the time from study enrollment to disease progression.

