Abbreviations: C1D1, cycle 1 day 1; C2-x, cycle two and subsequent cycles; CT, computed tomography; ECOG, eastern cooperative oncology group; EOT, end of treatment; HBV, hepatitis B virus; HCG, human chorionic gonadotropin; HCV, hepatitis C virus; HIV, human immunodeficiency virus; MRI, magnetic resonance imaging.

Footnotes.

a Cycle Definition: Each treatment cycle is 3 weeks. Assessments listed under the Treatment column are to be performed prior to drug administration on day 1 of cycle two and subsequent cycles. Cycle 1 day 1 assessments are covered under Screening.

b Physical Examination: Includes vital signs (blood pressure, heart rate, respiratory rate, temperature), height, and weight.

c HBV, HCV, and HIV, Test: Includes HBsAg, HBsAb, HBeAg, HBeAb, HBcAb, HCV, antibody, and HIV, antibody screening. Patients with positive HBsAg must undergo further quantitative HBV DNA, testing. Patients with positive HCV, antibody must undergo further quantitative HCV RNA, testing.

d Pregnancy Test: Only applicable to women of childbearing potential. A serum β-HCG, test must be performed within 7 days prior to the first dose and at the safety follow-up visit.

e Tumor Imaging: Contrast-enhanced CT, or MRI, of the chest, abdomen, and pelvis. Scans performed during Screening serve as the baseline. Subsequent scans are performed every 8 weeks (±7 days), until disease progression or withdrawal of consent. The same imaging modality should be used throughout the study.

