### Statistical analysis

2.7

The sample size is calculated based on a Simon’s two-stage optimum design. The null hypothesis (P0) assumes a historical ORR of 5% for second-line treatment, while the alternative hypothesis (P1) anticipates an ORR of 20%. With a one-sided alpha of 0.05 and a beta of 0.2, the first-stage enrollment is 10 patients (n1 = 10), with a futility boundary of 0 responders (r1 = 0). The total planned enrollment is 29 patients (n = 29), with a rejection boundary of three responders (r = 3). Accounting for a 10% dropout rate, the total enrollment target is 32 patients.

Analyses will follow the intention-to-treat principle. The full analysis set and per-protocol set will be used for efficacy, while the safety analysis set will cover all patients who received at least one dose of the study drug.

Continuous variables will be presented as mean ± standard deviation or median with range, and categorical variables as frequencies and percentages. ORR and DCR will be reported with 95% Clopper-Pearson confidence intervals. Time-to-event endpoints (OS, PFS, DoR, TTP) will be estimated using the Kaplan-Meier method. Univariate and multivariable Cox proportional hazards models will be used to explore the impact of baseline characteristics and biomarkers on survival outcomes. Multivariable Cox regression models will include prior treatment characteristics as covariates to adjust for potential heterogeneity in baseline therapies. All statistical tests will be two-sided with a significance level of 0.05, performed using SPSS version 22.0 or higher.

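### The measurable-disease criterion names RECIST 1.1 but adds size limits that differ by scanner, so a 10-19 mm lesion qualifies on spiral CT and fails on MRI

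*Protocol article*

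**What the plan says.** Four places in the protocol article bear on what counts as measurable disease.

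- **Section 2.3, text:** "Patients must possess at least one measurable lesion according to RECIST version 1.1". No size limits are given.
- **Section 2.3, Table 1, measurable-disease row:** it opens with "Presence of at least one measurable lesion according to RECIST v1.1" and then adds "Longest diameter ≥10 mm if measured by spiral CT or ≥20 mm if measured by conventional CT or MRI". The limits are in longest diameter for every lesion. Nodes are not mentioned.
- **Section 2.1:** the primary ORR is the proportion with CR or PR "according to Response Evaluation Criteria in Solid Tumors (RECIST) version 1.1".
- **Table 2, footnote e:** "Contrast-enhanced CT, or MRI, of the chest, abdomen, and pelvis. Scans performed during Screening serve as the baseline". Neither modality is preferred, and the footnote asks that the modality chosen be kept throughout the study.

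The article does not print the RECIST 1.1 size limits.

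**The concern.** Entry and endpoint should define measurable disease in the same way, because a response can only be scored on lesions that the endpoint criteria recognise. Here one table row carries two definitions. The first is RECIST 1.1, which is also the endpoint instrument. The second is a set of millimetre limits that depend on the scanner and treat nodes like any other lesion.

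Two things are at stake. First, patients may be accepted or refused according to a choice of scanner that the protocol otherwise leaves free. Second, if the printed limits displace RECIST 1.1 at screening, some entrants might have no target lesion on which a PR could be scored. That matters in a trial that stops if none of the first 10 patients responds and that needs four responses among 29 evaluable patients.

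**Working it through.** **Step 1. Apply the Table 1 limits to one lesion under each permitted modality.** The inputs are the two limits in Table 1 and the free choice of modality in footnote e.

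| Longest diameter | Spiral CT (limit 10 mm) | Conventional CT or MRI (limit 20 mm) |
|---|---|---|
| below 10 mm | not eligible | not eligible |
| 10-19 mm | eligible | not eligible |
| 20 mm or more | eligible | eligible |

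The middle row is the inconsistency. It follows from the article alone, and it holds whichever way the two sentences of the Table 1 row are combined.

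**Step 2. Set the two readings of the row side by side.**

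- *Both sentences apply.* A patient needs a RECIST 1.1 measurable lesion that also meets the printed limits. Someone without a RECIST 1.1 lesion fails the first sentence and is not enrolled. What remains is the refusal of 10-19 mm lesions on MRI.
- *The size sentence serves as the working definition.* The same refusals occur. In addition, a node that meets 10 mm in longest diameter on spiral CT would qualify, even if RECIST 1.1 would not accept it as a target lesion. This step assumes that RECIST 1.1 has a separate short-axis rule for nodes. That rule is not printed in the article and should be checked against the published standard.

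**Step 3. Reproduce the design.** The inputs from section 2.7 are P0 = 5%, P1 = 20%, one-sided alpha 0.05, beta 0.2, stage 1 rule 0/10 and final rule 3/29. The probability of rejecting the null is

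sum over x = 1 to 10 of P(X = x) × P(Y ≥ 4 − x), with X ~ Bin(10, p) and Y ~ Bin(19, p).

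This gives 0.0468 at p = 0.05 and 0.8011 at p = 0.20. A search for the optimal design under these inputs returns 0/10 and 3/29, so the printed design is correct. None of its inputs is a lesion size, so changing the row does not move it.

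**Step 4. Illustrate the conditional effect.** Suppose the second reading is used and such a patient can be scored neither PR nor CR.

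- All 10 stage 1 patients able to respond: 1 − 0.8^10 = 1 − 0.107 = 0.893.
- One of the 10 unable to respond: 1 − 0.8^9 = 1 − 0.134 = 0.866.
- Difference: 2.7 percentage points.

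The article gives no share of such patients, so the effect on overall power is shown over an assumed range. The effective ORR is 0.20 × (1 − f).

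| Assumed share f unable to respond | Effective ORR | Power |
|---|---|---|
| 0% | 20% | 0.80 |
| 5% | 19% | 0.77 |
| 10% | 18% | 0.73 |
| 20% | 16% | 0.64 |

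These figures show sensitivity and do not estimate what will happen in this trial.

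**The case against.** The strongest reply is that RECIST 1.1 is required twice in section 2.3, and nothing says that the size sentence replaces it. Read as an extra condition, it can only narrow entry. A reader might infer from the row that patients without a valid target lesion will be enrolled and that the ORR will be biased. The article does not support that inference. It depends on one of two readings, no frequency is given, and only the final 29 are described as evaluable, so such patients might be left out of that count. This part of the reply stands, and it is why the second effect is stated only as conditional.

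A second reply is that a limit specific to modality is not in itself a contradiction, and that the RECIST 1.1 limits are not in the article. That is fair as far as it goes. The finding does not need those limits: the row adds a scanner-dependent condition that the section text does not contain, while footnote e treats the scanners as interchangeable.

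A third reply is that a patient with a small lesion can be scanned by spiral CT and so qualify. This helps only in part. Footnote e wants one modality kept throughout, so a patient meant to be followed by MRI cannot simply qualify on CT and then switch.

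**Conclusion.** The point holds in a limited form. What is certain from the article is that a patient whose only lesion is 10-19 mm is eligible on spiral CT and refused on MRI, although either scan may serve as baseline. The number of patients affected is unknown, because the expected use of MRI and the distribution of lesion sizes are not stated.

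Entry without a lesion assessable for PR is possible only if the size sentence is used in place of RECIST 1.1. The fall from 89.3% to 86.6% rests on that reading, on exactly one such patient in stage 1, on no route to CR for that patient, and on a true ORR of 20% in the others. The sample size, the futility rule and the rejection boundary stand as printed. This is an inconsistency in one eligibility row, worth correcting because the row determines who enters the primary endpoint.

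**What to change.** Delete the size sentence from the measurable-disease row of Table 1, so that RECIST 1.1 is the only definition of measurable disease for both entry and response.

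If the sponsor prefers to keep numbers in the table for screening staff, replace the sentence with the RECIST 1.1 limits, copied from and checked against the published standard. As I understand that standard, this means one limit for CT and MRI at adequate slice thickness and a short-axis rule for nodes.

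The cost is one table line, with no new procedure and no change to the design. The downside is a slight shift in who is eligible: some patients imaged by MRI become eligible, and any patient who would have qualified only on a small node does not.

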### Recruitment and screening

2.4

Screening procedures will be conducted after obtaining informed consent (Table 2). These include the collection of demographic data, comprehensive medical history, a full physical examination encompassing height, weight, and vital signs, and ECOG performance status. Laboratory assessments will cover complete blood count, urinalysis, blood chemistry, coagulation, tumor markers, cardiac enzymes, thyroid function, and serology for hepatitis B virus (HBV), hepatitis C virus (HCV), and human immunodeficiency virus (HIV). Patients with positive HBsAg must undergo an HBV DNA test, and those with positive HCV antibodies requires an HCV RNA test. Women of childbearing potential must undergo a serum β-HCG test. Cardiac safety will also be assessed via electrocardiograms, and echocardiography. Tumor imaging will be performed using contrast-enhanced computed tomography (CT) or magnetic resonance imaging (MRI) of the abdomen, pelvis, and chest. Quality of life (QoL) scores will be recorded at baseline according to EORTC QLQ-C30 or QLQ-BIL21.

**TABLE 2 T2:** Schedule of patient visits and assessments.

Study period	Screening		Treatment		Follow-up	
Visit window *a*	Within 2 weeks prior to C1D1	Within 1 week prior to C1D1	Within 1 week prior to C2-xD1	Every 8 weeks ( ± 1 week)	4 weeks ( ± 1 week) after EOT	Every 12 weeks ( ± 1 week) after EOT
Clinical assessments						
Demographics	✓	​	​	​	​	​
Medical history	✓	​	​	​	​	​
Physical examination *b*	​	✓	✓	​	✓	​
ECOG performance status	​	✓	✓	​	✓	​
Quality of life	​	✓	​	✓	✓	​
Adverse events	​	​	✓	​	✓	​
Concomitant medications	✓	​	✓	​	✓	​
Electrocardiograms	✓	​	✓	​	✓	​
Echocardiogram	✓	​	​	​	✓	​
Laboratory assessments						
Complete blood count	​	✓	✓	​	✓	​
Urinalysis	​	✓	✓	​	✓	​
Blood chemistry test	​	✓	✓	​	✓	​
Coagulation test	​	✓	✓	​	✓	​
HBV, HCV, and HIV test *c*	✓	​	​	​	✓	​
Tumor markers test	​	✓	✓	​	✓	​
Cardiac enzymes test	​	✓	✓	​	✓	​
Thyroid function test	​	✓	✓	​	✓	​
Pregnancy test *d*	​	✓	​	​	✓	​
Tumor assessment						
CT/MRI imaging *e*	✓	​	​	✓	✓	​
Biomarker exploration						
Tumor sample	​	✓	​	​	​	​
Blood sample	​	✓	✓	​	​	​
Follow-up						
Survival status	​	​	​	​	​	✓
Subsequent therapy	​	​	​	​	​	✓

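### Read literally, the Table 1 bracket on childbearing potential leaves pre-menopausal women outside the contraception exclusion

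*Protocol article*

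**What the plan says.** Four places in the protocol article bear on this.

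- **Table 1, Pregnancy and lactation (section 2.3).** The row has two limbs. The first excludes "Women who are pregnant or breastfeeding". The second excludes "patients of childbearing potential (men or women who have been post-menopausal for less than 1 year) unwilling to use effective contraception methods".
- **Table 1, Demographics.** The inclusion rule is "Age between 18 and 75 years, male or female".
- **Section 2.4, Recruitment and screening.** "Women of childbearing potential must undergo a serum β-HCG test".
- **Table 2, footnote d.** The pregnancy test is "Only applicable to women of childbearing potential". It is due within 7 days before the first dose and again at the safety follow-up visit. The Table 2 grid agrees: the pregnancy-test row is marked in the screening column for the week before cycle 1 day 1 and in the column for 4 weeks after the end of treatment. Neither treatment column is marked.

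Section 2.2 lets treatment continue for up to 24 months.

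**The concern.** A bracket placed directly after a term is normally read as its definition, and the article gives no other. This one names men and women whose menopause was less than a year ago. A menstruating woman has not been post-menopausal for any length of time, so on the words alone she is not in the group that must be willing to use contraception.

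At stake is whether an eligibility rule bearing on patient safety can be applied as printed. Staff who check eligibility against the text would find that the contraception condition attaches to recently post-menopausal women and not to younger women, which is hard to square with the purpose of the clause.

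**Working it through.** No figure in the plan depends on this wording, so there is nothing to recompute apart from a rough count. The check is a reading of the passages against each other.

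1. **Whom the bracket covers.** Men, and women post-menopausal for less than 1 year. Women post-menopausal for 1 year or longer are left out, as one would expect. Pre-menopausal women are also not named.
2. **Whether pre-menopausal women can enrol.** Yes. The age range starts at 18 and both sexes are eligible. Nothing in Table 1 excludes women by menopausal status.
3. **Whether the other limb of the row closes the gap.** Only in part. It excludes women who are pregnant or breastfeeding at entry, whatever the bracket says. It does not deal with conception after entry, which is what the contraception limb is for.
4. **Whether testing closes the gap.** Not during treatment. The printed tests fall before the first dose and about 4 weeks after the end of treatment. Between them lie up to 24 months of treatment with no scheduled pregnancy test. In that interval the contraception exclusion is the only safeguard the article prints. This holds even if every pre-menopausal woman is tested at screening.
5. **Whether the test passages inherit the bracket.** Nothing in them says so. Section 2.4 and footnote d use the term without repeating the bracket or referring to Table 1. They also limit it to women, whereas the bracket includes men, so they do not simply reproduce the Table 1 group. In its ordinary meaning the term includes pre-menopausal women.
6. **Rough size.** The article gives no age or menopausal distribution. Assuming that 0% to 10% of the 32 patients are pre-menopausal women, the count is 0 × 32 = 0 to 0.10 × 32 = 3.2, that is 0 to 3 women. The percentages are an assumption, and the range includes none at all.

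**The case against.** The strongest reply is that nobody would apply the bracket literally. The governing words are those before it, and an investigator is unlikely to decide that a menstruating woman lacks childbearing potential. The bracket most plausibly garbles a reference to women who have not yet been post-menopausal for a full year, or was meant to extend the term to men and recently post-menopausal women. This stands as an account of the likely intent, and it is why the point is minor. It does not make the printed words right: eligibility is applied and audited as written. The row in Table 1 that allows exclusion on the investigator's judgement is discretionary and does not repair an explicit criterion.

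A second reply is that the article condenses a fuller protocol that is not shown, so the slip may exist only here. That is possible and cannot be settled from the article. But the point concerns a criterion that is printed and wrong as printed, not one left to another document.

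A reader might also infer something stronger: that pre-menopausal women drop out of the pregnancy test as well, so that pregnancies could go undetected at entry. The article does not support this. The test passages do not cite the bracket, the ordinary meaning of their wording includes these women, and pregnant women are excluded by a separate limb. The loss of testing would follow only if someone carried the faulty bracket across.

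**Conclusion.** The wording is defective and should be corrected. On its literal reading, the contraception exclusion omits pre-menopausal women who are otherwise eligible, and no other printed safeguard covers the time between the first and last pregnancy tests. That conclusion rests on the printed text alone, with the bracket taken as the definition of the term it follows.

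The point is minor. The intent is fairly clear, few patients are likely to be affected, and no endpoint, sample size, boundary or analysis depends on the wording. It is a drafting error in an eligibility criterion, not a flaw in the design. That women go untested for pregnancy is not established.

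**What to change.** Correct the Table 1 bracket so that it does not omit pre-menopausal women. Then reconcile Table 1, section 2.4 and Table 2 footnote d to one explicit definition, stated once and referred to in the other places. Any further clinical content of that definition is for the sponsor and the investigator.

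The change is about one sentence plus two cross-references. Compared with the literal reading, a few more women would have to agree to contraception in order to enrol, and any who were unwilling would be excluded. If the test passages already carry their ordinary meaning, no test is added. If a site had carried the bracket over, the few women concerned would gain the tests at the two time points already scheduled. No statistical figure changes.
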